### Statistical methods

Data will be entered into SAS version 9.2. Initial descriptive analyses will be used to describe the socio-demographic and disease characteristics of the participants. Independent t-tests (or other non-parametric equivalents) will be used to assess difference between the intervention and control groups. Paired t-tests (or other non-parametric equivalents) will be used to assess changes in outcomes from baseline to follow-up. Longitudinal data will be analyzed using generalized estimating equation (GEE) models. Analyses will take into account potential clustering of dyad behaviors. Potential mediators of PA behavior change will be assessed using a product-of-coefficients test.

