## Methods

### Study design

The study utilizes a two-arm randomized controlled trial design with a wait-list control group. Participants complete data collection at baseline, eight and 20 weeks. Intervention participants also complete these measures again at 12 months from baseline. The intervention consists of six, two-hour face-to-face group sessions held over eight weeks. Control group participants are invited to attend ENRICH after completion of the baseline, eight, and 20 week measures. Ethics approval was obtained from the University of Newcastle Human Research Ethics Committee (H-2009-0347). The design, conduct and reporting of this study will adhere to the Consolidated Standards of Reporting Trials (CONSORT) guidelines [33].

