### Setting

Three intervention programs and three control programs have been conducted in Sydney, New South Wales, Australia. A further four to six programs are planned to occur in 2011.

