### Intervention development and content

ENRICH consists of four weekly sessions, followed by two fortnightly sessions. Each session consists of a mix of healthy eating information and activities, a home-based walking program information and resources (with pedometer), and a home-based resistance training program (with elastic tubing equipment, Gymstick™) with information and resources.

ENRICH program sessions are co-facilitated by an exercise physiologist (exercise specialist) and dietician who received training from members of the research team. Educational information is supplemented with practical activities (eg. food label reading), group discussion (eg. brainstorming ideas to overcome barriers to being more active), and role modelling and practice of resistance training exercises, including stretching and appropriate warm-ups and cool down. The practice is to assist participants to become familiar and comfortable with the equipment, and allows the exercise physiologist an opportunity to ensure correct technique. Participants receive a pedometer, Gymstick™, step count diary, and written resources as part of the program.

A Gymstick™ http://www.gymstick.net is a lightweight graphite shaft, with elastic tubing and foot straps that provide resistance and can be used to exercise all of the major muscle groups. It is a safe, effective and relatively inexpensive tool for a strength-based exercise program to be conducted at home [52]. Gymsticks™ are available in five different resistance levels and the load on each device can be increased by rolling the bar and shortening the elastic tubing [52].

The program content was developed by experts in each of the content areas (members of research team), with input from advisory and working group members, and reviewed by oncology dieticians and physiotherapists. The program content is structured, but allows flexibility in the delivery to allow for discussion, questions, and interactive activities.

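### The analysis names dyads as its only source of clustering, although the intervention is given in a small number of co-facilitated groups; if outcomes correlate within a program, standard errors are understated

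*Protocol article*

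**What the plan says.** Statistical methods sets out the between-group comparison as "Independent t-tests (or other non-parametric equivalents) will be used to assess difference between the intervention and control groups". For repeated measures it adds: "Longitudinal data will be analyzed using generalized estimating equation (GEE) models". The one statement on non-independence is "Analyses will take into account potential clustering of dyad behaviors". Program group and facilitator are not mentioned there, and the sample-size section contains no design effect.

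Other sections describe how treatment is delivered. Study design says: "The intervention consists of six, two-hour face-to-face group sessions held over eight weeks". Intervention development and content says: "ENRICH program sessions are co-facilitated by an exercise physiologist (exercise specialist) and dietician". It also describes group discussion and shared practice of exercises. Setting gives the number of groups so far, "Three intervention programs and three control programs have been conducted in Sydney, New South Wales, Australia", and those to come, "A further four to six programs are planned to occur in 2011", without dividing the latter by arm. On the wait-list arm, Study design says: "Control group participants are invited to attend ENRICH after completion of the baseline, eight, and 20 week measures".

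**The concern.** People who attend the same program share two facilitators and a set of peers, and the intervention works partly through that contact. Their outcomes at 8 and 20 weeks may therefore be correlated. Controls are not in groups at those time points, so the design is partially nested: clustering by treatment group arises in the intervention arm alone.

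The plan recognises non-independence but names only the smaller unit. A dyad is usually two people, whereas a program would hold roughly 12 to 15. An independent t-test, or a GEE whose clusters are dyads, treats people in the same program but in different dyads as independent. If they are not, the variance of the intervention mean is understated, confidence intervals for the step-count difference and the secondary outcomes are too narrow, and the false-positive rate is above its nominal level.

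**Working it through.** **The plan's own figure.** Inputs from Statistical power and sample size: difference 2000 steps, SD 3200, power 80%, significance 5% (taken as two-sided).

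n per group = 2 × (3200/2000)² × (1.96 + 0.842)² = 2 × 2.56 × 7.85 ≈ 40.2, so 41. The exact noncentral-t calculation gives 42 (power 0.798 at 41 and 0.808 at 42). The stated 42 reproduces, and it assumes independent observations.

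**Number and size of programs.** Three intervention programs have been run. An even split of the further four to six adds 2-3, giving 5-6. If all of them were intervention programs the total would be 7-9. With the target of 75 per arm, 5-6 programs mean m = 75/5 = 15 or 75/6 = 12.5 people each.

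**Formulas.** The ICC is assumed, since the documents give none; the range used is 0 to 0.10. Dyad correlation is left aside to isolate the effect of program group.

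- Intervention-arm design effect: DE = 1 + (m − 1) × ICC. Control arm: 1.
- True SE / naive SE = √[(DE + 1)/2].
- True type I error = 2 × [1 − Φ(1.96 / SE ratio)].

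**Example.** With m = 15 and ICC = 0.05, DE = 1 + 14 × 0.05 = 1.70. The SE ratio is √(2.70/2) = 1.162. The type I error is 2 × [1 − Φ(1.96/1.162)] = 0.092.

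**Results, two-sided nominal 5%:**

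| ICC | 75 per arm, 6 programs | 75 per arm, 5 programs | 42 per arm, 6 programs | 42 per arm, 5 programs |
|---|---|---|---|---|
| 0 | 5.0% | 5.0% | 5.0% | 5.0% |
| 0.01 | 5.7% | 5.8% | 5.4% | 5.4% |
| 0.02 | 6.3% | 6.6% | 5.7% | 5.9% |
| 0.05 | 8.4% | 9.2% | 6.8% | 7.2% |
| 0.10 | 11.8% | 13.3% | 8.6% | 9.4% |

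At 75 per arm the SE ratio at ICC 0.05 is 1.135 (6 programs) or 1.162 (5 programs).

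**Checks.** Simulating the plain t-test at 75 per arm, 100,000 runs per scenario, gave 8.4% (6 programs) and 9.2% (5 programs) at ICC 0.05, and 5.0% for both at ICC 0.

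With more programs, 75 per arm and ICC 0.05:
- 7 programs: m = 10.7, DE = 1.486, SE ratio 1.115, type I error 7.9%.
- 9 programs: m = 8.33, DE = 1.367, SE ratio 1.088, type I error 7.2%.

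**Interval width after correction** (75 per arm, ICC 0.05). Satterthwaite df = (DE + 1)² / [DE²/(k − 1) + 1/74], where k is the number of programs.
- k = 5: 2.70² / (1.70²/4 + 1/74) = 7.29/0.736 ≈ 9.9. The critical t is about 2.23, against 1.976 for the naive test, so relative width is 1.162 × 2.23/1.976 ≈ 1.31.
- k = 6: 2.575² / (1.575²/5 + 1/74) = 6.63/0.510 ≈ 13.0. The critical t is about 2.16, so relative width is 1.135 × 2.16/1.976 ≈ 1.24.

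**The case against.** A reader might infer that the standard errors are bound to be too small and the error rate bound to exceed 5%. The documents do not support that. It requires a program ICC above zero, and none is given. Structured content, a home-based walking and resistance program and an individually measured step count could all keep it small. At ICC 0.01 the excess is under one percentage point. This objection stands, and the claim must be conditional. None of these features shows that the ICC is zero, however.

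A reader might also list season among the shared effects. It does not belong in the argument: both arms follow the same measurement schedule, and if they were recruited in parallel, season would largely cancel in the contrast. Only facilitator and peer effects support nesting in one arm.

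The mention of control programs might suggest that both arms are grouped. Study design places control attendance after the 20-week measures, so it does not affect the comparison.

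A further tempting reading is that the trial is underpowered. At 75 analysed per arm in 5-6 programs, power is still about 0.84-0.96 for ICC 0.01-0.10 (normal approximation, before attrition and few-cluster losses). At ICC 0.05 it would fall to about 0.75-0.76 if only 42 per arm were analysed, but 42 is the calculated minimum, not the recruitment target.

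Finally, this is a condensed article, and a fuller analysis plan could add program group without contradicting it. That lowers the severity. It does not remove the point, because the text addresses clustering explicitly and selects the smaller unit.

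**Conclusion.** The point holds in conditional form. Followed as written, the plan treats members of the same program as independent unless they belong to the same dyad. If the program ICC is above zero, the between-group standard error is understated.

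The size rests on three things the article does not fix: the ICC, the number of intervention programs and the number analysed. At ICC 0.05 the true error of a nominal 5% test is 8.4-9.2% with all 75 per arm analysed in 5-6 programs, 6.8-7.2% with 42 analysed per arm, and 7.2-7.9% with 75 analysed in 7-9 programs. The direction is the same throughout. This should be fixed before outcomes are analysed; it does not invalidate the design.

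**What to change.** Extend the clustering sentence to say that the between-group analysis accounts for ENRICH program group in the intervention arm as well as for dyad. A suitable specification is a partially nested linear mixed model with random effects for participant, dyad and, in the intervention arm only, program group, using Kenward-Roger or Satterthwaite degrees of freedom. This would replace the independent t-test as the basis for inference. A GEE sandwich variance at program level should not be relied on with so few programs. The estimated program ICC should be reported.

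The cost is a change of wording and a few lines of SAS code; the attendance records held by the Project Co-ordinator should identify program membership. The statistical price is more than cosmetic. At ICC 0.05 and 75 per arm in 5-6 programs, intervals would be about 24-31% wider than the naive ones once the small-sample degrees of freedom are used. The program variance itself will be imprecisely estimated.

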## Discussion

The ENRICH program meets a current gap in the provision of care to cancer survivors and carers, during the survivorship phase. The program focuses on important lifestyle behaviors that have the potential to address long-term and late effects of cancer and treatment, as well as prevention of other chronic health conditions. The program was intentionally developed to be applicable to cancer survivors diagnosed with different cancers and at different stages. The program has the ability to be individually tailored, and because it is not prescriptive, is relevant to all group members. The focus of the program is on giving participants the skills and knowledge to make achievable, life-long change appropriate to the ability of participants.

Limitations of the study include the reliance on self-report data for body composition and dietary behavior. It was not possible to obtain objective waist and weight measures from the control group participants, without potentially influencing their behaviors during the intervention period.

A novel approach of the program is the emphasis on self-management constructs, and provision of materials for a predominantly home-based PA program. Home-based activity programs place control back with participants who can exercise at a pace and ability at their own comfort level. The use of a home-based resistance training device is also a novel aspect of the program, with the efficacy of an elastic tubing device yet to be demonstrated in this population. As much as ENRICH is designed for participants to implement themselves at home, there is further potential for this program to be modified and tested in different formats that might be applicable to those disadvantaged through distance, isolation, or transport.

## Conclusion

With increasing numbers of cancer survivors at-risk for long-term and/or late effects of treatment and other chronic disease, efforts for promoting the health of this important group are urgently needed. This lifestyle program may provide valuable information relating to the development of other healthy lifestyle interventions for cancer survivors and carers, and result in appropriate behavior change and self-management strategies.

## List of abbreviations used

ENRICH: Exercise and Nutrition Routine Improving Cancer Health; PA: Physical activity; QoL: Quality of life; DQES: Dietary Questionnaire for Epidemiological Studies; BMI: Body mass index; heiQ: Health Education Impact Questionnaire; GEE: Generalized Estimating Equation.
